## Abstract

**Background:**

The morbidity of influenza in children increased rapidly in decade. Reduning injection (RDN), a small but fine Chinese herbal formula, has antipyretic, antiviral, anti-inflammatory effects. We intend to evaluate the efficacy and safety of RDN for the influenza in children versus Oseltamivir, explore the possible antiviral mechanism of RDN and provide evidence-based medical evidence for rational clinical drug usage.

**Method:**

We design a randomized, double-blind, double-dummy, parallel control of positive drug, multi-centre clinical study. According to the formula of mean superiority test, a total of 240 patients with influenza in children will be randomized 1:1 into the experimental group and control group. The experimental group will take RDN and Oseltamivir phosphate granule simulants and the control group will take Oseltamivir phosphate granule and RDN simulants. Each group will be treated for 5 days. The primary outcome measure is temperature recovery time, and the secondary outcome measures include time when the fever begins to subside, time and degree of disease to alleviate, disappearance rate of individual symptoms and so on. We will measure before enrollment and each 24 h after treatment for comparison.

**Discussion:**

The study is launched to evaluate the efficacy and safety of RDN for the treatment of influenza in children and to provide an alternative option for influenza in children.

**Trial registration:**

This study is registered in ClinicalTrials.gov as NCT04183725, registered on 3 December, 2019.

**Supplementary Information:**

The online version contains supplementary material available at 10.1186/s12906-023-04037-1.

## Introduction

Influenza, a negative-strand RNA virus of the Orthomyxoviridae family, is classified into influenza A, B and C viruses (IAV, IBV and ICV). Specially, with its “reassortment” of segmented genomes [1], IAV is easily to cause a pandemic in human. Influenza virus invades respiratory tract usually in winter leading to acute infectious disease accompanied by characteristic symptoms of fever suddenly, cough, chills or sweats, myalgia and malaise [2, 3]. Infectious disease was the most important cause of death in children under 5 years [4], and young children were the major targets of influenza comparing with older counterparts [5]. Children under 5 years had the highest rates of influenza-associated hospitalizations and Influenza-like illness (ILI) outpatient visits [6]. Besides, the age composition ratio from 2010 to 2019 of discharge patients in China indicated that influenza population under 14 years ranged from 33.3% grow into 78.5% [7]. Consequently, the direct and indirect burden on society and family has increased a lot compared to before [8].Therefore, one of the most urgent issues is how to response to influenza in children effectively to reduce the burden.

Fever, occurring in 95% of influenza children, is the most salient sign, 59% of children 3 years has fever 39.0℃ [9]. Fever outdoes all others and is the only reliable predictor of influenza virus infection [10]. We selected time of temperature recovery as the primary measure to evaluate treatment effect. Time when fever begins to subside is also included as a secondary outcome to observe when RDN starts to work. Apart from fever suddenly, clinical features of ILI such as cough, chills, running nose, sore throat, headache, myalgia and so on are common clinical manifestations [9, 11, 12]. So clinical symptom record table and score of each symptom are developed to record time and degree of disease alleviation to understand the change of disease. The disappearance rate of individual symptoms will be recorded after medication to evaluate RDN’s effect on each symptom. Although clinical manifestations are typical for diagnosis, laboratory testing is necessary too [13]. So we select rapid antigen test [14] to estimate negative conversion rate of influenza viral and detect its type [2]. Special circumstance such as symptomatic treatment needs to be considered, thus we will record number and frequency of antipyretic and analgesic drugs if using. Children < 5 years are likely to develop severe complications (age < 2 years easier) [15], hence we will monitor incidence of complications of influenza to ensure children’s safety.

Reduning (RDN), consisting of Qing Hao (*sweet wormwood herb*), Zhi Zi (*fructus gardeniae*) and Jin Yin Hua (*honeysuckle*), is a traditional Chinese medicine injection under patent protection (Chinese patent number CN201711264903.0). RDN treats influenza virus through alleviating pulmonary inflammation and reducing inflammatory factors release [16]. Meanwhile RDN has been recommended to treat H7N9 influenza infection [17]. A case of 108 patients of influenza in adult, RDN has a comparable effect with Oseltamivir but faster work and short course [18]. We intend to evaluate efficacy and safety of RDN to provide a possible therapeutic strategy for influenza in children. Oseltamivir (Kewei) is the recommended drug for influenza in children approved by *Influenza Diagnosis and Treatment Program (2018 Edition)* [15] and *Recommendations for Prevention and Control of Influenza in Children (2016–2017)* [19], so we choose it as positive control to reflect the superior curative efficacy and safety of RDN objectively.

## Method

### Study design

This is a randomized, double-blinded, double-dummy, parallel control of positive drug, multi-centre clinical study. The trial will be conducted in ten centers at China and collaborate with hospitals including Children’s Hospital Of Soochow University, Anhui Provincial Children’s Hospital, Qilu Children’s Hospital of Shandong University, Tianjin 4th Centre Hospital, Renmin Hospital of Wuhan University, Hebei Maternity&Child Healthcare Hospital, the Second Affiliated Hospital of Jiaxing University, the First Hospital of Hunan University of Chinese Medicine, Affiliated Hospital of Shanxi University of Traditional Chinese Medicine and one undetermined. The trial obtained ethical approval from Ethics Committee of The First Affiliated Hospital of Henan University of Chinese medicine (approval number: 2019HL-137-01), and will be conducted according to *the World Medical Association Declaration of Helsinki* and *Good Clinical Practice of Pharmaceutical Products* [20, 21].

Participants with influenza in Children will undergo a standardized baseline evaluation before treatment. All included participants are randomly divided into two groups: experimental group and control group.The experimental group receives RDN + Oseltamivir phosphate granule simulants and the control group receives Oseltamivir phosphate granules + RDN simulants. After five days of treatment with evaluation every 24 h, the efficacy and safety of two groups will be evaluated. The study design is shown in Fig. 1.

**Fig. 1 Fig1:**
[figure not shown]
Flow diagram

### Sample size estimation and randomization

Taking time of temperature recovery as clinical main efficacy indicator, we calculate two groups’ sample size using mean superiority test formula. According to data of efficacy evaluation about adult influenza treating with RDN and Oseltamivir in the early stage, the per protocol set (PPS) of time of temperature recovery comes: Oseltamivir is 46.50 ± 1.74(h) and RDN is 30.47 ± 1.69(h); so that δ for 15.35 h, 100 participants will be required for each group, and 200 is the total. If the 20% dropout rate is considered, 240 cases were planned to be observed. We adopt the method of center stratified block randomization in trial: there is 10 centers, 4 segments, each center has 24 cases and each group has 12 cases.

Randomization will be used for patient allocation [22]. The randomization will be performed by an independent statistician. The random numbers are divided into two groups sequentially: experimental group and control group. SAS 9.1.3 statistical software will be used for seed number, and randomized grouping tables will be generated for the 240 patients receiving treatment. During the trial, the investigator will be able to obtain the randomized number and drug number of each patient from the designated central randomized platform. All random numbers grouped are sent to each trial center and corresponding treatment kits are provided.

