### Statistical method

Data analysis will be performed by professional statisticians using SAS 9.1.3. For measurement data, Group t test or Wilcoxon rank sum test will be used for comparison between groups; for counting data, χ^2^ test and Fisher exact test will be used, Rank sum test and Cochran Mantel Haenszel (CMH)test will used for grade data; for efficacy indicators, PPS analysis and FAS analysis will be used at the same time. The statistical analyses will use the two-sided hypothesis test. P ≤ 0.05 will be set as the significant level.

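### The 100 per group follows from a 15.35 h superiority margin that the written analysis never uses, and from ± values that may be standard errors

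*Protocol article*

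**What the plan says.** Under Sample size estimation and randomization, the article takes time of temperature recovery as the main efficacy indicator and says "we calculate two groups’ sample size using mean superiority test formula". The planning values are per-protocol results from earlier adult data: "Oseltamivir is 46.50 ± 1.74(h) and RDN is 30.47 ± 1.69(h". The conclusion follows directly: "so that δ for 15.35 h, 100 participants will be required for each group, and 200 is the total". The section does not define δ and gives neither a significance level nor a power. Dropout is then added: "If the 20% dropout rate is considered, 240 cases were planned to be observed".

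Under Statistical method, the comparison is described as "For measurement data, Group t test or Wilcoxon rank sum test will be used for comparison between groups", and the error level as "The statistical analyses will use the two-sided hypothesis test. P ≤ 0.05 will be set as the significant level". Analysis contents adds covariance analysis with centre for measurement data. Neither section mentions a margin, and nor does the definition of the primary outcome.

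**The concern.** The sample size and the analysis appear to address different hypotheses. The size fits a trial meant to show that RDN is faster by more than 15.35 h. The analysis, as written, is an ordinary comparison of two groups. A reader cannot tell whether a significant primary result would establish any benefit or a benefit above 15.35 h, nor what power the trial has for either.

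The spread is a second problem. A value of about 1.7 h is very small for a recovery time averaging 30 to 46 h, and every power statement depends on it.

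**Working it through.** **Inputs.** Means 46.50 and 30.47 h, ± values 1.74 and 1.69 h, δ = 15.35 h (Sample size estimation and randomization). Two-sided 5% (Statistical method). 1:1 allocation (abstract). Power is not stated; 80% is tried first.

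**1. Planning difference.** 46.50 − 30.47 = 16.03 h. Excess over δ: 16.03 − 15.35 = 0.68 h.

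**2. Reproducing the plan's figure, with δ as a superiority margin.**

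n per group = (z₀.₉₇₅ + z₀.₈₀)² × (SD₁² + SD₂²) / (difference − δ)²

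= (1.96 + 0.8416)² × (1.74² + 1.69²) / 0.68²

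= 7.849 × 5.8837 / 0.4624 = 99.9, so 100.

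At 85, 90 and 95% power the same formula gives 115, 134 and 166. Of these conventional levels only 80% fits.

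**3. Same inputs, test of no difference.**

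- Difference 16.03 h: 7.849 × 5.8837 / 16.03² = 0.18, so 1 per group.
- Difference 15.35 h: 7.849 × 5.8837 / 15.35² = 0.20, so 1 per group.

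For 100 per group to be the 80%-power size against zero, the SD would have to be about 40.5 h (difference 16.03 h) or 38.7 h (15.35 h). The article gives no such SD.

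**4. Fragility of the margin sizing.** The numerator is 46.18. An excess of 0.78 h gives 46.18 / 0.78² = 75.9 per group, and an excess of 0.58 h gives 46.18 / 0.58² = 137.3. A shift of 0.1 h moves the size that far, on an outcome that after 24 h need only be read twice a day in this trial.

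**5. Are the ± values patient-level SDs?** The root mean square of 1.74 and 1.69 is 1.715 h, so the assumed effect is 16.03 / 1.715, about 9 SDs, with almost no overlap between arms. That is implausible, and standard errors are a natural explanation. *Assumption:* standard errors from 40 to 60 patients per arm.

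| Assumed patients per arm in adult data | SD = 1.715 × √n | Needed per arm, 15.35 h margin, 80% power | Needed per arm, 16.03 h against zero, 80% power |
|---|---|---|---|
| 40 | 10.8 h | 3,995 | 8 |
| 54 | 12.6 h | 5,394 | 10 |
| 60 | 13.3 h | 5,993 | 11 |

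Power with 100 per arm at SD 12.6 h: the standard error of the difference is 12.6 × √(2/100) = 1.78 h. Against the margin, 0.68 / 1.78 = 0.38, and P(Z > 1.96 − 0.38) is about 6%. Against zero, 16.03 / 1.78 = 9.0, so power is over 99.9%.

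**6. Detectable difference.** A 20% loss from 240 leaves 192, or 96 per arm. At 80% power the detectable difference is 2.8016 × SD × √(2/96) = 0.404 × SD: 5.1 h at SD 12.6, 10.1 h at SD 25, 16.2 h at SD 40.

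**The case against.** The best defence is that the figure of 100 is arithmetically exact. The article says it used a superiority formula, and in such a formula δ is naturally a margin. A two-sided test does not exclude a margin either: the 95% interval from the covariance analysis could be compared with 15.35 h, and an analysis plan not shown here might say so. The Statistical method section is a generic list and never states a null of zero.

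Much of this stands. It shows that the arithmetic is not at fault, and that the supportable claim is that the margin is not carried into the written analysis. It does not remove the mismatch: the article prints both the sizing basis and the tests, and only the sizing implies a margin.

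Four stronger readings are tempting and are not supported:

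- *That 15.35 h is a miscalculated difference.* The article never calls it the difference.
- *That ±1.7 h cannot be patient-level SDs.* Evenly spaced 12-hourly readings would add a rounding SD of 12/√12 = 3.5 h. But that schedule is a minimum for this paediatric trial, and the adult data's schedule is not given.
- *That the SD is too small by a factor of about 7.* That is √54. It needs the ± values to be standard errors, and the source to be the 108-patient adult study cited in the Introduction, split equally with everyone in the per-protocol set. The sample-size section does not make that link.
- *That the trial is too small.* Against zero, 100 per arm is ample on either reading of the ± values, if the assumed 16.03 h holds.

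**Conclusion.** The point holds as an inconsistency between the sample-size basis and the written analysis. Given the stated ± values as SDs, 100 per group comes only from a margin test at 15.35 h with 0.68 h to spare. That margin is about 96% of the assumed effect (15.35 / 16.03) and appears nowhere in the outcome or analysis sections. This conclusion rests on one inferred input, 80% power.

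That the ± values are implausible as patient-level SDs is a judgement; that they are standard errors is a possibility the documents do not settle. The contrast of about 6% power against the margin (4,000 to 6,000 per arm needed) with over 99.9% against zero depends on that reading and on the assumed 40 to 60 patients per arm. It shows how much hangs on which hypothesis is meant. It matters because the stated justification for the trial's size cannot stand beside the stated analysis.

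**What to change.** Rewrite the sample-size paragraph:

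1. State the primary hypothesis. Either make it a two-sided 5% test of no difference and drop the 15.35 h margin from the sizing, or, if a margin is meant, write it into the primary analysis and justify it.
2. Check against the adult data whether the ± values are SDs or standard errors, and plan with the patient-level SD.
3. State that the planning difference is 16.03 h and define the role of δ. State the power used.
4. For a test of no difference, keep 240 and report the power, or the difference detectable at 80% power, with 96 evaluable per arm over a plausible range of SDs in children, using the figures in step 6 of the working.

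The cost is a wording change and a recalculation. The no-difference option needs no extra patients, though the justification becomes less tidy. The margin option would need the size reworked if the ± values prove to be standard errors.

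### The 20% dropout allowance is added on (200 × 1.2 = 240) when it should be divided out (200 / 0.80 = 250), so at 20% dropout 192 patients remain, 8 short of the 200 required; a minor slip affecting the per protocol set or completers

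*Protocol article*

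**What the plan says.** The section on sample size estimation and randomization of the protocol article sets the requirement first: "100 participants will be required for each group, and 200 is the total". The allowance for losses follows at once: "If the 20% dropout rate is considered, 240 cases were planned to be observed". The same total is built into the allocation scheme, where "there is 10 centers, 4 segments, each center has 24 cases and each group has 12 cases". The abstract repeats it ("a total of 240 patients with influenza in children will be randomized 1:1"), and so does the Discussion.

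The planning data are earlier adult results, introduced with the words "the per protocol set (PPS) of time of temperature recovery comes". The paragraph gives a mean and a ± value for each drug and adds "so that δ for 15.35 h". It does not say whether δ is an effect to be detected or a margin, and it states no power.

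Three other sections matter here:

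- Under Statistical method, efficacy is analysed in both the full analysis set and the per protocol set, with two-sided tests at 0.05.
- The notice that closes Exit criteria keeps every dropout in the full data set, using the last result obtained.
- Discontinuation records children with no improvement or with aggravation after three days or more as treatment failures within the per protocol set.

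**The concern.** The paragraph gives a required number, a dropout rate and a planned total, and the three do not fit together. A loss of 20% is taken from the patients who are enrolled, so the enrolled number has to be divided by 0.80 to recover the requirement. Adding 20% to the requirement gives a smaller total and leaves the trial short at the very rate it claims to cover.

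The sample size would then not deliver what the article says it needs. The planning means come from a per protocol set, and the per protocol set is one of the two efficacy analysis sets, so it is fair to read the 200 as patients who remain after losses. The word evaluable is not in the article, which says only that the patients are required. Making an allowance at all, however, implies that dropouts are not counted towards the 200.

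**Working it through.** **Inputs**, all from the section on sample size estimation and randomization unless marked:

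- Required: 100 per group, 200 in total
- Dropout rate: 20%
- Planned total: 240, as 10 centres × 24, with 12 per group in each centre
- Oseltamivir 46.50 ± 1.74 h and RDN 30.47 ± 1.69 h, with ± read as SD (an assumption)
- δ = 15.35 h
- Two-sided tests at 0.05 (from Statistical method)

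**Step 1. Reproduce the plan's figure.** 200 × (1 + 0.20) = 240. This matches exactly.

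**Step 2. The number that keeps 200 after 20% dropout.** 200 / (1 − 0.20) = 250, or 125 per group. The plan is 10 below this.

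**Step 3. What 240 leaves at 20% dropout.** 240 × 0.80 = 192, or 96 per group. That is 8 short in total and 4 short per group.

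**Step 4. The dropout rate that 240 does cover.** 1 − 200/240 = 40/240 = 16.7%.

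| Dropout | Left of 240 | Per group | Against 200 |
|---|---|---|---|
| 10% | 216 | 108 | +16 |
| 15% | 204 | 102 | +4 |
| 16.7% | 200 | 100 | 0 |
| 20% | 192 | 96 | −8 |

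**Step 5. Size in power, under stated assumptions.** The article gives no power and does not define δ, so both have to be assumed.

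- Difference in means: 46.50 − 30.47 = 16.03 h.
- Pooled SD: √((1.74² + 1.69²)/2) = 1.715 h.
- *Assumption A: 15.35 h is a superiority margin and the design power is 80%.* The difference left to detect is 16.03 − 15.35 = 0.68 h. Then n per group = 2 × (1.960 + 0.842)² × 1.715² / 0.68², just under 100, which rounds up to the 100 stated. Normal-approximation power is 80.1% at 100 per group and 78.4% at 96. With the t distribution it is 79.7% and 78.0%. The loss is 1.6 to 1.7 percentage points.
- *Assumption B: 15.35 h is a plain effect to be detected.* The same formula gives 1 per group, which does not reproduce 100. Power is practically 100% at both 96 and 100 per group, so the shortfall costs nothing.

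Only assumption A recovers the stated 100 per group. That makes it the likelier reading of the calculation, but the article does not confirm it.

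**The case against.** **Adding 20% to the requirement is a common shortcut.** That is so, but the article calls the 20% a dropout rate and nowhere defines it as an add-on. At that rate the shortcut does not return the required number. No other section gives a separate reason for 240.

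**Dropouts are not all lost.** This largely stands. The Exit criteria notice keeps every dropout in the full data set with the last result, so the shortfall does not carry over to that analysis. Discontinuation also keeps treatment failures in the per protocol set. What remains is a shortfall among completers or in the per protocol set.

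**A reader might infer that 20% attrition is to be expected, given the list of exit rules.** The documents do not support that. They report no observed dropout rate, and worsening after three days, one of the listed exits, does not by itself take a child out of the per protocol set. Other exits, such as poor compliance, unblinding or prohibited drugs, could do so, but nothing says how often. Below 16.7% dropout there is no shortfall at all.

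**A reader might also infer that the trial is underpowered.** That does not follow either. The drop from about 80% to about 78% needs assumption A, and the Statistical method section describes ordinary two-sided comparisons without mentioning a margin. The undefined δ is a separate and larger weakness of the same paragraph; it does not change the dropout arithmetic.

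**The planned number suits the layout.** This stands. 240 divides into 24 per centre and 12 per group, whereas 250 would mean 25 per centre, which cannot be split equally between two groups within a centre.

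**Conclusion.** The statement is wrong as written: 200 required, 20% dropout and 240 planned cannot all hold. The correct total for those inputs is 250, and 240 leaves 192 (96 per group) at 20% dropout. This conclusion uses only figures printed in the article, plus the usual meaning of a dropout rate as a share of those enrolled.

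The consequence is minor. It is confined to the per protocol set or completers, it arises only if dropout exceeds 16.7%, and at 20% it amounts to 4 patients per group. In power it is worth less than 2 percentage points if 15.35 h is a superiority margin and 80% power was intended, and practically nothing if 15.35 h is a plain effect. The documents do not support a claim that the trial is underpowered, that dropout will reach 20%, or that recruitment has to rise.

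**What to change.** Keep 240 and the layout of 24 per centre, and replace the dropout sentence with one along these lines: *240 randomised patients leave 200 (100 per group) at up to 16.7% dropout, and 192 (96 per group) at 20%.* Say that these numbers refer to completers or the per protocol set.

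If a power figure is given alongside, state what it rests on: the role of 15.35 h, the difference left to detect, the SD, the two-sided 0.05 level and the intended power. On the superiority-margin reading (0.68 h, SD 1.715 h, intended power 80%), the figures to quote are about 80% at 100 per group and about 78% at 96. Until δ and the design power are defined, the power should be left out or marked as conditional.

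The cost is one sentence and a slightly less favourable stated figure, with no extra patients and no change to randomisation, centres or analysis.
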